## Abstract

**Introduction:**

von Willebrand Factor (vWF) is a key protein mediating platelet adhesion on the surface of damaged endothelia. To the best of our knowledge, no trial exists that investigated the effect of platelet transfusion in combination with the administration of balanced vWF in severe blood loss, despite being widely used in clinical practice. The Basel Will-Plate study will investigate the impact of the timely administration of balanced vWF (1:1 vWF and FVIII) in addition to platelet transfusion on the need for blood and coagulation factor transfusion in patients admitted to the intensive care unit (ICU) who suffer from severe bleeding. The study hypothesis is based on the assumption that adding balanced vWF to platelets will reduce the overall need for transfusion of blood products compared to the transfusion of platelets alone.

**Methods and analysis:**

The Will-Plate study is an investigator-initiated, single-centre, double-blinded randomised controlled clinical trial in 120 critically ill patients needing platelet transfusion. The primary outcome measure will be the number of fresh frozen plasma (FFP) and red blood cell (RBC) transfusions according to groups. Secondary outcome measures include the number of platelet concentrates transfused within the first 48 h after treatment of study medication, quantity of blood loss in the first 48 h after treatment with the study medication, length of stay in ICU and hospital, number of revision surgeries for haemorrhage control, ICU mortality, hospital mortality, 30-day mortality and 1-year mortality. Patients will be followed after 30 days and 1 year for activities of daily living and mortality assessment. The sample size was calculated to detect a 50% reduction in the number of blood products subsequently transfused within 2 days in patients with Wilate® compared to placebo.

**Ethics and dissemination:**

This study has been approved by the Ethics Committee of Northwestern and Central Switzerland and will be conducted in compliance with the protocol, the current version of the Declaration of Helsinki, the ICH-GCP or ISO EN 14155 (as far as applicable) and all national legal and regulatory requirements. The study results will be presented at international conferences and published in a peer-reviewed journal.

**Trials registration:**

ClinicalTrials.gov NCT04555785. Protocol version: Clinical Study Protocol Version 2, 01.11.2020. Registered on Sept. 21, 2020.

**Supplementary Information:**

The online version contains supplementary material available at 10.1186/s13063-022-06876-8.

## Strengths and limitations of the study

The study’s main strength is the implementation of a promising and secure therapy approach for patients suffering from severe bleeding.This is a prospective, randomised, double-blind, placebo-controlled clinical trial for data of high-quality evidence.The study is limited by the heterogeneity of critically ill patients and therefore the underlying causes of bleeding. However, bleeding sources will be documented.

## Background and rationale

Von Willebrand factor (vWF) represents a key protein produced by the endothelial cells as a heterogeneous mixture of low- and high-molecular-weight units. vWF is a ligand for receptors on the platelet surface and endothelial cells (GPIb-V-IX, αIIbβ3, αvβ3) mediating adhesion of platelets to each other or to the surface of damaged endothelium and supporting platelet activation. Initial platelet adhesion is a crucial step in haemostatic function [1, 2]. It plays also an important role in protecting FVIII from early activation and clearance^1^.

Several vWF preparations exist (e.g. Wilate, Hemate-P, Alphanate, Wilfact, Veyvondi), the majority of which are combined with antihaemophilic factor (coagulation factor VIII). The product’s included coagulation factor VIII acts in the activated form like the regular factor VIIIa. It takes part in the coagulation amplification by activating factor X to Xa together with factor IXa. Activation of factor X results in generating thrombin from prothrombin. With the administration of both products—von Willebrand factor and coagulation factor VIII—thrombocyte function and overall coagulation may be improved. Wilate® is a 1:1 balanced mixture of von Willebrand factor and coagulation factor VIII registered in Switzerland for prophylaxis and treatment of bleeding in patients suffering from von Willebrand disease and haemophilia A.

There is suggestive evidence from an in vitro flow chamber model and from the treatment of patients with severe vWF deficiency that increasing the concentration of vWF onto normal or supranormal levels can enhance platelet adhesion independent from platelet count [4]. This might translate into a better haemostatic effect of administered platelet concentrates in the bleeding patient and less need for transfusion of blood products (platelet concentrates), especially in clinical conditions with a high probability of low platelet count and low-vWF activities (e.g. heart surgery with extracorporeal circulation or patients under extracorporal membrane oxygenation (ECMO)).

To the best of our knowledge, no trial exists that investigated the effect of platelet transfusion in combination with the administration of balanced vWF in patients with a need for platelet transfusion, despite being widely used in our clinical practice. With this trial, we will investigate if timely administration of balanced vWF (1:1 vWF and FVIII) in addition to platelet transfusion can increase haemostatic efficacy and reduce the transfusion of allogeneic blood products and the need for additional coagulation factor concentrates.

## Hypothesis

In the randomised Will-Plate study, we aim to test the hypothesis that a single simultaneous transfusion of platelets and balanced vWF concentrate reduces the overall need for transfusion of blood products compared to transfusion of platelets alone (i.e. compared to placebo) with a functional focus on platelet concentrates.

## Methods

### Study design

The Will-Plate study is an investigator-initiated, single-centre, prospective, randomised, double-blind, placebo-controlled clinical trial of patients suffering from severe blood loss.

### Approvals

Approval to conduct this study was granted by the Ethics Committee of North-western and Central Switzerland (EKNZ 2020-02106) in December 2020 and by the Swiss Agency for Therapeutic Products (Swissmedic, 2021DR4037) in March 2021. This study was registered at the Swiss National Clinical Trial Portal (SNCPT; Identifier: SNCTP000004204) and at ClinicalTrials.gov (Identifier: NCT04555785).

### Study setting

Patients from the intensive care unit of the University Hospital of Basel are primarily scheduled for study participation. This is an adult ICU at a Swiss academic tertiary medical centre treating medical or surgical patients.

### Study population

#### Inclusion criteria

Participants fulfilling all of the following inclusion criteria are eligible for the study:Age ≥ 18 yearsAdmission to the intensive care unit (ICU)Patients needing platelet transfusion with or without severe bleeding or prior treatment with single or dual antiplatelet agents (ASS, prasugrel, clopidogrel, ticagrelor)Consent by the patient or a family member (non-emergency cases) in addition to the statement of an independent ICU physician

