## Study period overview

All patients needing platelet transfusion will be screened for study eligibility (Fig. 1). Upon enrolment, recruited patients will be randomised to one of the two treatment arms (i.e. platelet transfusion with vWF or placebo) with consecutive ICU follow-up for 2 days (Table 1). It will not be allowed to administer another dose of Wilate®/placebo for the study period of 48 h after the first dose was given.

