### Screening

Patients will be recruited at the ICU after cardiac surgery, multiple trauma, ECMO or (other) diseases going along acute clinical bleeding at the time of thrombocyte transfusion prescription.

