### Experimental intervention

Wilate® is a 1:1 balanced mixture of von Willebrand factor and coagulation factor VIII. It belongs to the group of anti-haemorrhagic and coagulation factors. It is extracted from plasma, freeze-dried and virus-inactivated by two steps. In Switzerland, it is registered to prevent and treat bleeding of patients suffering from haemophilia A and von Willebrand disease. It is administered as dry solid, which has to be dissolved with the included solvent (water for injection including 0.1% polysorbat 80).

The vWF of the product acts like the vWF of human plasma. It is a key protein mediating platelet adhesion on the surface of damaged endothelial cells or collagen, initiating platelet-platelet aggregation and supporting platelet activation. It plays also an important role in protecting FVIII from early activation and clearance.

The product’s coagulation factor VIII acts in the activated form like the regular factor VIIIa. It takes part in the coagulation amplification by activating factor X to Xa with factor IXa as a co-factor. Activation of factor X generates thrombin from prothrombin.

Wilate® is approved in Switzerland for prophylaxis and treatment of bleeding in patients suffering from von Willebrand disease and haemophilia type A.

In case of haemorrhage and indicated platelet transfusion, a study package will be prepared by an unblinded site member and afterwards provided to the participating patient’s physician in charge with one dose of Wilate® (2000 IU vWF and 2000 IU factor VIII and water for injection including 0.1% polysorbat 80) or placebo (replenished with sodium chloride 0.9%). Additionally, one platelet concentrate provided by the blood bank of the University Hospital of Basel will be ordered. Platelet components are either single donor apheresis or buffy-coat pooled platelet components, pathogen-reduced and containing at least 2.4 × 10e11 platelets per unit.

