## Definitions/conditions

### Inclusion criteria

Adult medical and surgical patients admitted to the ICU who need platelet transfusion with or without severe bleeding (i.e. needing transfusion of at least 2 ECs) will be included.

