#### Pre-existing thrombocyte/vWF disorders

Patients suffering from innate or acquired platelet disorder (i.e. HIT, TTP, HUS, ITP, sepsis, haemato-oncological disease, other hereditary thrombocytopathies)—with the exception of prior treatment with single or dual antiplatelet agents—or disease affecting vWF (i.e. von Willebrand disease, haemophilia A) will be excluded from the study in order to be able to reliably assess the effect of vWF when added to platelets.

Hypersensitivity to the active substances is defined as a known allergy to vWF or a substance contained in the placebo.

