## Adherence to intervention protocols

Each time a platelet concentrate is prescribed, a red flag will appear in our data monitoring system. The vWF kit from Basel (HemosIL^2^) will be used to measure the vWF activity (vWF:Ac). The vWF:Ac is measured at four individual times per patient: baseline, 30 min after the thrombocyte concentrate administration has ended, the following day at 6 AM and the day after at 6 AM.

Because the study medication is only a few millilitres and should be given at least 5 min before giving platelets, handling it only for a few minutes will be enough to get it to room temperature, so the study medication will be kept in the fridge until randomisation.

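### The eligibility texts are inconsistent: three platelet disorders excluded in the definitions are missing from the exclusion list, and whether bleeding is required, and how severe it must be for dosing, is not settled.

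*Protocol article*

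**What the plan says.** **Exclusions.** The Exclusion criteria list under Study population is presented as the operative one: any single item excludes the patient. For platelet disorders it names HIT, TTP, HUS and known inherited thrombocytopathies. It also excludes patients given vWF/FVIII concentrate before inclusion, with no time limit.

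Under Definitions/conditions, the section on pre-existing thrombocyte/vWF disorders excludes inborn or acquired platelet disorders, spelled out as "i.e. HIT, TTP, HUS, ITP, sepsis, haemato-oncological disease, other hereditary thrombocytopathies". Its reason is scientific: "in order to be able to reliably assess the effect of vWF when added to platelets". Another section under the same heading limits the prior-concentrate exclusion to the preceding 48 h.

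**Bleeding.** The inclusion criterion under Study population is "Patients needing platelet transfusion with or without severe bleeding or prior treatment with single or dual antiplatelet agents". The version under Definitions/conditions covers adult ICU patients "who need platelet transfusion with or without severe bleeding (i.e. needing transfusion of at least 2 ECs) will be included". The intake is broad: "Each time a platelet concentrate is prescribed, a red flag will appear in our data monitoring system" (Adherence to intervention protocols) and "All patients needing platelet transfusion will be screened for study eligibility" (Study period overview).

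Other sections assume a bleeding patient. Screening recruits after cardiac surgery, multiple trauma, ECMO or other "diseases going along acute clinical bleeding at the time of thrombocyte transfusion prescription". Experimental intervention says "In case of haemorrhage and indicated platelet transfusion, a study package will be prepared by an unblinded site member" and gives stopping the haemorrhage as the aim of treatment. The Hypothesis under Statistics is stated for patients with clinical bleeding. Study design goes further and describes the population by severe blood loss, and Study medication has the drug given once in the event of severe bleeding.

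**The concern.** Eligibility rules decide who is randomised. Under Datasets to be analysed, every included patient is analysed by intention to treat unless consent is withdrawn retrospectively, so a patient admitted under the wrong rule is not removed later.

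The three missing conditions are plausible here. The Study setting is an adult ICU treating medical as well as surgical patients, where someone with sepsis or haemato-oncological disease may well need platelets. The protocol itself says that such patients stand in the way of a reliable assessment of the vWF effect.

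On bleeding, a patient given platelets without bleeding would lie outside the statistical hypothesis, yet no inclusion criterion turns that patient away explicitly. A patient with minor bleeding is eligible, but Study medication makes the dose conditional on severe bleeding.

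**Working it through.** No arithmetic beyond a count applies, so the texts are set side by side.

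**Step 1: exclusions.**

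| Condition | Exclusion criteria list | Pre-existing thrombocyte/vWF disorders |
|---|---|---|
| HIT | yes | yes |
| TTP | yes | yes |
| HUS | yes | yes |
| Inherited thrombocytopathies | yes | yes |
| ITP | no | yes |
| Sepsis | no | yes |
| Haemato-oncological disease | no | yes |

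Seven conditions are named in the definitions and four are on the list: 7 − 4 = 3 missing. None of the three falls under the list's item on inherited disorders. The list does name some acquired conditions (HIT, TTP, HUS and, separately, overt DIC), so the gap is these three diagnoses and not acquired disease as a whole.

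**Step 2: is the second text only a definition?** The section on prior concentrate shows what a definition looks like in this article: it puts a 48 h window on an item already listed. The section on platelet disorders does something else. It adds diagnoses that the list does not contain.

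**Step 3: bleeding.** Three readings of the inclusion criterion can be tested.

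| Reading | Agrees with | Conflicts with |
|---|---|---|
| No bleeding needed | Study period overview; the red-flag rule | Screening; Experimental intervention; Hypothesis (Statistics); Study design; Study medication |
| Bleeding of any severity needed | Screening; Experimental intervention; Hypothesis (Statistics) | Study design; Study medication |
| Severe bleeding needed | Study design; Study medication | Both Inclusion criteria sections |

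The middle reading fits best, but the inclusion criteria do not state it, and it leaves one conflict. Take a bleeding patient who needs fewer than 2 ECs, the threshold for severe bleeding under Definitions/conditions. That patient is eligible. Table 1 places randomisation and study medication together at time 0. Study medication, however, gives the drug in the event of severe bleeding. No reading reconciles all of these sections.

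**The case against.** The strongest reply on exclusions is that the two sections should be read together, so that a condition in either place excludes the patient. The list nowhere says that a patient with ITP, sepsis or haemato-oncological disease is eligible. Eligibility is also checked in the eCRF before randomisation (Randomisation section), and the content of that check is not shown. This stands in part: the text supports that staff could enrol such patients, not that they would. It does not remove the fault, because the list is presented as the operative one and is incomplete. A related point also stands: sepsis is named as an example of a platelet disorder, so it is unclear whether sepsis alone excludes a patient.

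On bleeding, the reply is that Screening and Experimental intervention act as the filter after a broad flag and a broad screen, and that the inclusion wording merely admits less severe bleeding. That is a fair reading and takes much of the force from this half. A reader might infer that the trial definitely sets out to enrol non-bleeding patients; the documents do not support that. What remains is that the bleeding requirement is left unstated and that severe bleeding is written as a condition for dosing.

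It can also be said that requiring bleeding is a choice, since the other sections could instead be aligned to need for platelets alone. That is true, but it would mean changing the hypothesis and the stated aim of treatment.

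**Conclusion.** The exclusion mismatch is a contradiction within the article and not a detail left to a fuller document, since both rules are printed and select different patients. Its size is three of seven named disorders; confidence is high. The bleeding half holds in the narrower form above, with moderate confidence. Both should be fixed.

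Two stronger inferences are tempting and are not supported. A reader might conclude that the trial loses power. That would need the share of affected patients and the mean and dispersion of the transfusion count, none of which the article gives, so neither a loss of power nor an error in the total of 120 is shown. A reader might also suspect that the 150 historical patients behind the sample size were drawn from a different population. Determination of sample size says that they meet the inclusion criteria, and nothing in the text suggests otherwise.

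**What to change.** 1. Use one exclusion list, in the Exclusion criteria section and in the eCRF eligibility check. Add ITP, sepsis and haemato-oncological disease, state whether sepsis alone excludes, and give the 48 h window for prior vWF/FVIII concentrate.
2. In both Inclusion criteria sections, require clinical bleeding of any severity at the time of platelet prescription, matching Screening and the Hypothesis under Statistics.
3. Remove severe bleeding as a condition for dosing in Study medication and severe blood loss as the population descriptor in Study design, so that every randomised patient is dosed as in Table 1. Similar descriptive wording elsewhere, such as in the Abstract, Ethical justification and Discussion, can follow.

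The cost is a wording amendment and an updated eCRF check. Recruitment may be slightly slower, and the trial would give no inference for platelet transfusion in patients who are not bleeding.

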#### Exclusion criteria

The presence of any one of the following exclusion criteria will lead to exclusion of the participant:Patients receiving factor vWF/VIII concentrate before inclusion in the study (e.g. Haemate®, Wilate®)Women who are pregnant or breastfeedingParticipation in another study with an investigational drug within the 30 days preceding and during the present studyOvert disseminated intravascular coagulation (DIC)Heparin-induced thrombocytopenia (HIT)Thrombotic thrombocytopenic purpura (TTP) or haemolytic uremic syndrome (HUS)Patients with known inherited thrombocytopathies or inherited coagulation disorders, including known von Willebrand disease or haemophilia APrevious enrolment into the current studyContraindications to the class of drugs under study, e.g. known hypersensitivity or allergy to the class of drugs or the investigational product

## Study period overview

All patients needing platelet transfusion will be screened for study eligibility (Fig. 1). Upon enrolment, recruited patients will be randomised to one of the two treatment arms (i.e. platelet transfusion with vWF or placebo) with consecutive ICU follow-up for 2 days (Table 1). It will not be allowed to administer another dose of Wilate®/placebo for the study period of 48 h after the first dose was given.

**Fig. 1 Fig1:**
[figure not shown]
Study flow chart

**Table 1 Tab1:** Study overview

***Visit***	***Screening***	***Treatment***	***Assessment***	***ICU follow-up***		***30-day and 1-year follow-up***^***b***^
*Time (hours, days, weeks)*	*− 1 h*	*0*	*30–60 min*	*1 day*	*2 days*	*12 months*
*Patient information and informed consent*	*x*^*a*^	*x*^*a*^	*x*^*a*^	*x*^*a*^	*x*^*a*^	
*Demographics*	*x*					
*Medical history*	*x*					
*In-/exclusion criteria*	*x*					
*Vital signs*	*x*		*x*	*x*	*x*	
*Platelet function analysis*	*x*		*x*			
*Laboratory tests*	*x*		*x*	*x*	*x*	
*Pregnancy test*	*x*					
*Randomisation*		*x*				
*Information related to bleeding*	*x*		*x*	*x*	*x*	
*Study medication*		*x*				
*Primary outcome variable*			*x*	*x*	*x*	
*Secondary outcome variables*			*x*	*x*	*x*	*x*
*Adverse events*			*x*	*x*	*x*	
*Mortality* *ICU* *Hospital* *30 days* *1 year*				*x*	*x*	*x*

^a^If not possible so far

^b^Assessment of ICU and hospital length of stay, ICU and hospital mortality, 30-day mortality, 1-year mortality, and estimated costs of blood transfusion products

### Screening

Patients will be recruited at the ICU after cardiac surgery, multiple trauma, ECMO or (other) diseases going along acute clinical bleeding at the time of thrombocyte transfusion prescription.

### Thirty-day and 12-month follow-up

Survivors of critical illness not only suffer from long-term disability but also reduced long-term survival [5–7]. To assess the long-term follow-up of patients who received vWF and compare it to those who received placebo, we will perform a follow-up at 30 days and 12 months after the prevailing hospital case has been officially closed (discharge date). With this follow-up, we will assess the following information equally at 30 days and 12 months (information either given by the patient or his/her family/contact person):Death after hospital dischargeHospital readmission

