#### Other secondary outcomes

Secondary outcome variables like ICU mortality, ICU length of stay, hospital mortality, hospital length of stay, number of bleeding events and number of revision surgeries/re-interventions for haemorrhage control are part of the routine clinical assessment for all hospitalised patients and will be documented accordingly. Patients or their family members will be contacted to assess the rehospitalisation rate, as well as 30-day and 1-year mortality.

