##### Mortality

Time-to-event analysis (cox proportional hazard regression) evaluates the difference between the study groups, adjusted for age, disease scores (simplified acute physiology score (SAPS II), sequential organ failure assessment (SOFA score)) and reason for ICU admission.

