### Handling of missing data and drop-outs

The number of dropouts and missing data for the primary and secondary endpoints will be low as the necessary information will be captured during the hospital stay. No complicated treatment regime is in place and the observation period is only 2 days for the primary endpoint.

To assess 1-year mortality, a hospital-wide process based on the AHV number (Swiss social security number) to capture the information from the governmental registry has already been implemented. Patients without a valid AHV number will be contacted personally.

In case of missing covariates, we will apply multiple imputation techniques and perform sensitivity analysis to show that missing information does not change the results of this trial in a substantial way. The main results will be reported based on complete cases.

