## Ethical justification

Due to the nature of the condition investigated (severe bleeding representing an emergency setting), patients eligible for study participation will not able to give their consent in most cases. As described above, we will seek the patient’s approval for use of collected data for our publication as soon as feasible.

Severe bleeding is a serious condition calling for immediate intervention. Because ICU length of stay is associated with patient morbidity and mortality we chose to investigate a therapeutic approach that might reduce the need for transfusion products and their possible side effects, thus, leading to shorter ICU and hospital stays and overall better outcomes.

By achieving our goal, we may positively influence patient well-being and enhance satisfaction after severe medical conditions and, most importantly, promote a reduction in patient morbidity and mortality. This in turn would have a positive impact on our society and on the economy.

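### The only origin stated in words for the follow-up tied to 30-day and 1-year mortality is hospital discharge, which conflicts with Table 1 and makes the window depend on length of stay

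*Protocol article*

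**What the plan says.** All references are to the protocol article.

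- **Thirty-day and 12-month follow-up** sets the clock: "we will perform a follow-up at 30 days and 12 months after the prevailing hospital case has been officially closed (discharge date". The stated purpose is to compare patients given vWF with those given placebo. Two items are collected: death once the patient has left hospital, and readmission.
- **Other secondary outcomes** links contact with patients to the endpoints: "Patients or their family members will be contacted to assess the rehospitalisation rate, as well as 30-day and 1-year mortality". It also says that ICU and hospital mortality, among others, "are part of the routine clinical assessment for all hospitalised patients and will be documented accordingly".
- **Table 1, footnote b**, attached to the column for the 30-day and 1-year follow-up, lists "Assessment of ICU and hospital length of stay, ICU and hospital mortality, 30-day mortality, 1-year mortality". The time axis of that table has randomisation and study medication at 0, then 30–60 min, 1 day, 2 days and 12 months.
- **Secondary outcome measures** lists mortality in ICU, in hospital, at 30 days and at 1 year, without an origin.
- **Secondary analyses, Mortality**: "Time-to-event analysis (cox proportional hazard regression) evaluates the difference between the study groups", adjusted for age, disease scores and reason for admission. No time zero is given.
- **Handling of missing data and drop-outs**: "To assess 1-year mortality, a hospital-wide process based on the AHV number (Swiss social security number) to capture the information from the governmental registry" is in place. Patients without a valid number are contacted personally.
- **Planned analyses** makes every analysis intention-to-treat, on all included patients unless consent is withdrawn retrospectively.
- **Ethical justification** hopes for an effect on stay: "leading to shorter ICU and hospital stays".

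**The concern.** The protocol is not silent here. It states a clock and a death item for the follow-up that carries two mortality outcomes, and both depend on something that happens after randomisation.

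Two consequences follow if the wording is applied as it stands. First, a patient who dies in hospital is never discharged, so a death item limited to the period after discharge describes hospital survivors only. That does not fit the intention-to-treat statement. Second, even with in-hospital deaths added back, the window runs from randomisation to discharge plus 30 days. Its length then depends on length of stay, which is itself a secondary outcome that treatment is hoped to shorten. An arm that leaves hospital sooner is observed for less time.

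Readers will take 30-day and 1-year mortality to mean time since randomisation or treatment. An analyst working from the axis of Table 1 and one working from the follow-up section would compute different endpoints.

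**Working it through.** The protocol gives no mortality or length-of-stay figure, so there is nothing to reproduce. The check is mainly of wording. The arithmetic illustrates direction and rough size, and every rate and stay in it is an assumption.

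**Three endpoints the text allows**

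- A. Deaths within 30 days (or 12 months) after discharge only: the follow-up section read literally.
- B. All deaths up to 30 days (or 12 months) after discharge: the same clock, with recorded in-hospital deaths added.
- C. All deaths within 30 days (or 12 months) of time 0 on the axis of Table 1.

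Only the discharge origin is put in words. C rests on the layout of a table.

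**A against B.** Take 60 patients per arm (from the sample size section), in-hospital mortality h and mortality q in the 30 days after discharge.

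- Post-discharge deaths = 60 × (1 − h) × q. All deaths = 60 × h + 60 × (1 − h) × q.
- With h = 20% vs 10% and q = 5% in both arms:
  - A: 60 × 0.80 × 0.05 = 2.4 vs 60 × 0.90 × 0.05 = 2.7.
  - B: 12 + 2.4 = 14.4 vs 6 + 2.7 = 8.7.
- Over h from 10% vs 5% to 30% vs 20%, and q from 2% to 5%, B runs from 7.1 vs 4.1 to 20.1 vs 14.4. Under A each arm has between 0.8 and 2.9 deaths, and the arms differ by at most about 0.3.

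Under A an in-hospital difference disappears. The small reversal in counts arises only because more survivors are at risk in the better arm; the risk among survivors is equal by assumption.

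**Share of deaths before discharge.** With d the mortality in the year after discharge, the share of all deaths up to that point that occur in hospital is h / (h + (1 − h) × d).

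- h = 15%, d = 15%: 0.15 / 0.2775 = 54%.
- h = 25%, d = 10%: 0.25 / 0.325 = 77%.

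**B against C.** Suppose stay after randomisation is 14 days in one arm and 10 in the other, and treatment has no effect on death.

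- The 30-day window ends on day 14 + 30 = 44 vs day 10 + 30 = 40.
- At a constant hazard of 0.002 per day, cumulative risk is 1 − exp(−0.002 × 44) = 8.4% vs 1 − exp(−0.002 × 40) = 7.7%.
- With a fixed 30-day window from randomisation it is 1 − exp(−0.002 × 30) = 5.8% in both arms.
- With stays of 30 and 20 days the risks are 11.3% and 9.5%. With equal stays of 20 days both are 9.5%, so the gap comes from the clock alone.
- For the 12-month window the same 4-day difference matters far less: 14 + 365 = 379 vs 10 + 365 = 375 days, about 1%.

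**The case against.** The best defence is that the follow-up section describes when people are telephoned, not how an endpoint is defined. Survivors and families are asked about death after discharge because earlier deaths are already known. Most of the supporting evidence stands:

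- In-hospital deaths are recorded as ICU and hospital mortality, and footnote b lists them beside 30-day and 1-year mortality.
- The contact is not the main source of 1-year status. The registry is.
- The axis of Table 1 points to treatment as the origin.
- The mortality analysis compares the study groups and nowhere restricts itself to patients discharged alive.
- An unstated Cox origin is, by itself, a detail the protocol may leave to its analysis plan.

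A reader might therefore be tempted to infer that in-hospital deaths drop out of the trial and that the comparison is no longer randomised. The documents do not support that. They show a rule that would have this effect if applied literally, not that the planned analysis will apply it so.

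The defence does not remove the point. No sentence says that in-hospital deaths count towards 30-day or 1-year mortality, or from which day. The registry supplies vital status, not an origin, and it is named for 1-year mortality only; for 30-day mortality the article describes only the contact. Table 1 contradicts the follow-up section and does not settle the matter.

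**Conclusion.** The point holds as an internal conflict and a badly fixed time origin. The only worded origin for the follow-up tied to 30-day and 1-year mortality is discharge, with a death item confined to the time after it, while Table 1 measures from treatment. Used as written, the rule would condition on surviving to discharge. Used with in-hospital deaths restored, it would give the arms unequal windows if their stays differ. The second effect matters mainly for 30-day mortality and is close to negligible at one year.

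The size is unknown. The percentages and death counts above rest wholly on assumed mortality, stay and hazard. The unequal window also needs a difference in stay, which the protocol hopes for but does not quantify.

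Two secondary mortality outcomes are affected. The 48-hour primary outcome and the sample size of 120 are not.

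**What to change.** - Define 30-day and 1-year mortality as death from any cause within 30 and 365 days of randomisation, in-hospital deaths included, for all intention-to-treat patients.
- Start the Cox model for mortality at randomisation as well.
- Take dates of death from the hospital record and the registry process, with personal contact where there is no valid social security number. Confirm that the registry process returns a date of death, which the protocol does not say; such a date would settle 30-day status too.
- Keep the discharge-timed contact for readmission and status after discharge, and label it so.
- Bring Table 1 with footnote b, the follow-up section, the other secondary outcomes, the mortality analysis and the missing-data section into line with this definition.

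The cost is a few sentences in the protocol and analysis plan. The sources of death information are already in place, since the process "to capture the information from the governmental registry has already been implemented". The wording should be settled before unblinding.
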